### Allocation to Study Arm

The two treatment arms (multidimensional active rehab and EGE progression) are assigned at random to the 28 sites in the study. Site level (cluster) randomization is utilized because the study team considered that patient-level randomization at a site would be prone to contamination between arms. Thus, all athletes at a given site receive the same protocol. All study sites are randomized to either the MDR (early rehabilitation) or the EGE [current return to sport strategy (16)]. To ensure a balanced of treatment arms across cohort, site randomization is stratified by (i.e., conducted within) cohort (NZR, CFL, College, HS). Colleges/universities and high school sites are stratified by size of school prior to randomization; CFL and NZR sites are not stratified. Due to the nature of the early and active treatment delineation, no allocation concealment such as masking or blinding is possible. The clinicians (site personnel) at the sites know their allocated arm. However, participants are not explicitly told about the role of their respective study arm. Site personnel at the MDR sites are trained to deliver the treatment separately from the site personnel at the EGE sites.

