***Specific Aim 1***
*(evaluation of effectiveness):* For analyses of our primary endpoints, Cox proportional hazards regression models (35) will be used to compare time to return to play and time to asymptomatic between the EGE and MDR groups. The specific outcomes for the Cox models will be time from date of injury to: (1) date of medical clearance for full return to participation and (2) asymptomatic date. The Wei-Lin robust variance estimator will be used to account for the effect of cluster-randomization by site (36).

For our secondary endpoints (clinical and quality of life measures), recovery trajectories will be examined by use of General Linear Mixed regression models and non-parametric smoothers. Random effects will be utilized to account for the effect of clustering by site and the effect of repeated observations over time within an individual participant. The time axis to be modeled in both sets of analyses is time from initiation of the treatment (defined as stable symptoms for 24 h), and time will be treated as a continuous variable in all analyses.

We will also assess potential predictors of attrition (e.g., gender, race, socioeconomic status). If no predictable patterns are observed for missing data (i.e., missingness occurs at random), no imputations will be conducted. Inverse probability of attrition weights based on the factors influencing attrition will be used to account for potential selection bias due to attrition. We will assess the differences between the EGE and MDR group participants (those with SCR) at baseline and before starting the treatment protocol.

For sensitivity analyses of primary and secondary, we will conduct intent-to-treat analysis (prescribed treatment), per-protocol analysis (adhered treatment) and use inverse probability weighting to determine potential outcomes had everyone adhered to their prescribed treatments.

To test the effectiveness of randomization, we will compare key variables at baseline and immediately post-injury (24-48 h timepoint) to determine differences between arms. These variables at a minimum will include: age, gender, previous history of concussion, contact/collision sport, baseline symptom severity score, 24–48 h symptom severity score. Should any differences be observed these factors will be controlled for in the models. Additionally, 24–48 h symptom severity will be considered in all analyses.

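### The primary Cox model as described names neither randomisation stratum and picks covariates by observed imbalance; the power cost runs from nil to about 14 points, depending on how prognostic cohort is

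*Protocol article*

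**What the plan says.** On allocation, the Protocol article (Allocation to Study Arm) says that the arms "are assigned at random to the 28 sites in the study", that "site randomization is stratified by (i.e., conducted within) cohort (NZR, CFL, College, HS"), and that "Colleges/universities and high school sites are stratified by size of school prior to randomization; CFL and NZR sites are not stratified".

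On the primary analysis (Planned Data Analysis, Specific Aim 1), "Cox proportional hazards regression models (35) will be used to compare time to return to play and time to asymptomatic between the EGE and MDR" arms, and "The Wei-Lin robust variance estimator will be used to account for the effect of cluster-randomization by site (36"). No stratum or fixed covariate list is attached to this model. The mixed models for the secondary endpoints name random effects for site and participant only.

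On covariates, the same section says: "To test the effectiveness of randomization, we will compare key variables at baseline and immediately post-injury (24-48 h timepoint) to determine differences between arms". It lists, as a minimum, age, gender, concussion history, contact or collision sport, baseline symptom severity and 24–48 h symptom severity. The rule follows: "Should any differences be observed these factors will be controlled for in the models". The next sentence adds that 24–48 h severity is to be considered in every analysis, without saying in what form.

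**The concern.** Two features work together. First, the factors that restricted the randomisation do not appear in the model described. If cohort predicts recovery time, stratified allocation makes the arms more alike than simple allocation would. An analysis that ignores the strata leaves the between-cohort variation in the site-level variance and gives that gain away. The article itself gives reason to expect cohort differences: *Varied Models of Clinical Care* describes different front-line providers by country and different standard protocols by governing body, and clearance, a primary endpoint, is decided by site clinicians.

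Second, the stated route for covariates into the model is an observed difference between arms. A difference between arms does not show that a variable is prognostic, and a strongly prognostic variable may be well balanced. Without a criterion for a difference, and with an open-ended list, two analysts could follow the text and fit different primary models. Cohort and school size are not on the list. If they were added, balance by design would tend to keep them out.

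At stake are power in a trial with little to spare and a primary model that can be known before the data are seen.

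**Working it through.** **1. The plan's own figure.** The Sample size paragraph gives 83% power with 100 per arm and a ratio of 4.5/7 (0.64). Schoenfeld's formula is power = Φ(|ln HR| × √(d/4) − 1.96). Two-sided 5% is assumed, since the article states no alpha. With 12.5% loss (the midpoint of the stated 10–15% attrition), d = 200 × 0.875 = 175. Then |ln(4.5/7)| = 0.442, √(175/4) = 6.61, 0.442 × 6.61 − 1.96 = 0.96, and Φ(0.96) = 83.2%. The other numeric cells of Table 4 are then within 1 point. With all 200 events the result is 87.8%. The 83% is therefore what an individually randomised comparison gives with no stratum, covariate or cluster term.

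**2. Effect of leaving cohort out.** From the article: 28 sites (9 Canadian football, 5 New Zealand rugby, 6 college, 8 high school), randomised within cohort; 200 injured athletes; Cox model with site-robust variance; effect 7/4.5 = 1.56 in the direction of faster recovery. Assumed: site log-hazard SD 0.2, symptom-severity log hazard ratio 0.5 per SD, about 12–15% censoring, and four equally spaced cohort effects with the SD shown. The extreme cohorts lie 2.68 SD apart, so their hazard ratio is exp(2.68 × SD). There were 1,000 trials per setting, with a Monte Carlo standard error of about 1.6 points for a power near 50%. School size was not simulated. Each pair of figures is without strata → stratified by cohort.

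| Cohort SD | HR, extreme cohorts | Type I error, % | Power at 1.96, % | Power at equal type I error, % | Gain, points |
|---|---|---|---|---|---|
| 0 | 1.0 | 8.1 → 9.9 | 65.7 → 68.0 | 53.4 → 53.6 | 0.2 |
| 0.15 | 1.5 | 5.5 → 9.4 | 56.4 → 63.8 | 53.9 → 54.7 | 0.8 |
| 0.3 | 2.2 | 5.1 → 10.3 | 50.2 → 69.6 | 49.9 → 54.6 | 4.7 |
| 0.6 | 5.0 | 1.5 → 9.3 | 23.8 → 67.0 | 41.1 → 55.0 | 13.9 |

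The last column is the fair measure. The nominal gaps of 2, 7, 19 and 43 points mix real gain with the difference in type I error between the two tests.

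**3. Whether the imbalance rule makes up the loss.** With covariates entered when the arms differed at p < 0.05 (an assumed threshold), no strata, five further weaker covariates and 600 trials, nominal power was 46% against 44% unadjusted at cohort SD 0.3, and 18% against 17% at SD 0.6. Gains of 2 and 1 points are within simulation error and far below the nominal gaps of 19 and 43.

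**4. Whether the rule inflates type I error.** In a separate set of runs (same sites, 200 athletes, site SD 0.2, six covariates entered at p < 0.05, 1,000 trials per setting), type I error unadjusted against imbalance-selected was 8.1 v 7.7%, 7.2 v 6.8%, 6.6 v 6.0% and 3.2 v 2.6% for cohort SD 0, 0.15, 0.3 and 0.6. No inflation appears. The excess over 5% is there without selection.

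**5. What the remedy does under the planned variance.** Type I error with strata alone was 9.3–10.3%; with strata and severity, 10.1–11.7%; with strata and six fixed covariates (the separate runs), 10.6–12.2%. At equal type I error, adding severity to the strata raised power to 65.9, 62.5, 64.7 and 65.6%, that is by 12.3, 7.8, 10.1 and 10.6 points over strata alone, under the assumed severity effect.

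**The case against.** The strongest reply is that the article is condensed. It does not exclude cohort or school size, and an unseen analysis plan may include both. That stands for the strata taken alone, and a reader who infers that the trial will certainly be analysed without them goes beyond the text. It does not reach the covariate rule, which the article states outright and which an analysis plan would inherit.

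Second, comparing the arms is not idle here. Sites are randomised, their clinicians know the arm, consent is individual and site staff diagnose the injury that starts the protocol. A difference between arms may reveal differential recruitment or identification, so the usual objection to testing a known randomisation applies only in part. This supports keeping the comparison as a check. It does not support building the model from it.

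Third, 24–48 h severity is named for all analyses whatever the imbalance. That softens the point, though considering a variable does not fix it as a covariate.

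Fourth, a reader might infer that selection by imbalance makes the p-values too small. The runs in step 4 of the working do not support that.

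Finally, the unstratified hazard ratio lies somewhat nearer 1. One simulation with cohort effects and no further site variation gave a mean log hazard ratio of 0.41 against a true 0.442, or 1.51 against 1.56. That is a marginal rather than a conditional effect, which is a legitimate target in a pragmatic trial, and is not counted as a fault.

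**Conclusion.** The point holds in a limited form. The model as described names neither stratification factor, and the stated covariate rule has no threshold, selects on imbalance rather than prognosis and leaves the final model open until the data are seen. In simulation it recovered almost none of the power lost by omitting a prognostic cohort.

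At equal type I error the loss is between nothing and about 5 points for a cohort log-hazard SD of 0 to 0.3, and about 14 points at 0.6. At 0.6 the unstratified test is also conservative (1.5% type I error in one set of runs, 3.2% in the other). The article gives no recovery times by cohort, so where the trial lies in this range is unknown. The figures also rest on the assumed site variation, severity effect and censoring.

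A larger loss is tempting to infer from the nominal gaps of 19 and 43 points, or from comparing an unstratified robust Cox test with a stratified Cox model tested by re-randomisation (64% v 76% with 200 athletes, 77% v 97% with 400, no further site variation, one assumed set of cohort effects). The first compares tests with different type I error. The second changes model and test together. Neither measures what stratification alone would gain.

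**What to change.** - Stratify both primary Cox models by cohort, with school size as a term within the college and high-school cohorts. Add cohort to the mixed models.
- Replace the imbalance rule with a short covariate list fixed in advance from variables already collected, including baseline and 24–48 h symptom severity. State that 24–48 h severity is a fixed covariate.
- Keep the between-arm comparison at baseline and 24–48 h as a descriptive check, including for differential recruitment or identification after site allocation.
- Specify a small-cluster correction to the robust variance, or a re-randomisation test that permutes sites within the strata actually used. This must accompany the first two changes: strata with the uncorrected robust variance would put type I error at about 9–12% with 28 sites.

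The cost is a few sentences, a few degrees of freedom and slightly more analysis work. With only 28 clusters the covariate list should stay short. No new data are needed.

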To address this gap, we are conducting a pragmatic cluster-randomized trial with two parallel groups. Of note, the trial was designed in 2016 and the outcomes and interventions selected were based on the following factors most relevant and applicable at that time: (1) common data elements in large-scale concussion studies (15); (2) pragmatic assessments and exercises that would apply in a variety of settings and that do not require extensive resources; and (3) logical intersection with the current return to sport paradigm. The trial includes athletes of varying age and levels of skill, from multiple countries, from multiple sports, and across multiple care models to understand the influence of early activity in the context of the return to sport strategy on outcomes following sport-related concussion. The two Specific Aims for this trial are to: (1) evaluate the effectiveness of the enhanced graded exertion (EGE) progression (current return to sport strategy) vs. an early, activity rehabilitation [multidimensional rehabilitation (MDR)] strategy; and (2) evaluate the safety and feasibility of these protocols.

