### Safety Procedures

As with any trial, safety-related procedures were decided *a priori* by the study team in concordance with current literature. Potential risk of the study assessments and interventions were evaluated. Based on previous studies and clinical fortitude, it was determined *a priori* that discomfort is likely (10–25%) to occur as the participants are progressed in the interventions. We specifically anticipated more discomfort among those in the multidimensional activity group, as discomfort may increase slightly during rehabilitation sessions, as often occurs within any type of rehabilitation session. All rehabilitation is monitored and progressed by medical professionals and individuals are referred to their team physician as deemed medically appropriate. If at any point the participant or clinician feels the intervention should be discontinued, this is done and documented. Injury risk is rare, however, there is the small possibility that symptom exacerbation or injury may occur during the interventions or testing. As all participants will be studied and progressed in environments with medical professionals, any potential significant symptom exacerbation or injury is documented, and participants are referred to the physician at the institution as deemed appropriate. The physician and medical team at each site will determine status and ability to continue the study activities. All events of this nature are documented appropriately via study administrative forms. A symptom-based adverse event was determined to be, as outlined in the progression, if an individual's symptoms increased by a reliable change of 10 or more points and remained elevated at that change in the subsequent session. An independent safety officer reviews quarterly study safety reports provided by the study team study and provides feedback on any overall concerns or safety issues. If the safety officer deems the study unsafe after corrective actions have been put into place, the study will be halted, or significant changes may be made to the study methods.

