### Study Outcomes and Assessments

The primary trial endpoints include time to asymptomatic/symptom free and time to full clearance for return to sport, in days. The secondary endpoints include clinical and quality of life outcomes assessed from baseline through 1-month post return to play, as well as safety and feasibility outcomes. An assessment protocol similar to the NCAA-DOD Grand Alliance Concussion Assessment, Research, and Education (CARE) Consortium's is utilized for both baseline measurements and post-injury assessments and to achieve the primary and secondary endpoints (15). The assessment time-points for the study (Table 3) include: pre-season baseline, time of injury (optional, 24–48 h following injury, daily symptom and activity tracking through 7 days post-return to play, athlete satisfaction at 7 days post-return to play, and 1-month following full return to play. Each of the assessment timepoints are collected at the approximate windows, i.e., within 5 days, due to the nature of athletic schedules. Study measures are administered by trained site personnel and clinicians. Assessments take place at site medical and training facilities. Below are brief descriptions of all study measures.

**Table 3 T3:** Assessment schedule.

	**Demographics**	**Personal and family history**	**SCAT symptom checklist**	**QOL**	**BSI-18**	**Neurocognitive assessment**	**SAC**	**BESS**	**NPC**	**Dual-task**	**Start and end fatigue rating**
**Pre-season baseline**	✓	✓	✓	✓	✓	✓	✓	✓	✓	✓	✓
**Time of injury (within 6 h—if possible)**			✓				✓	✓			
**24–48 h post-injury**			✓		✓	✓	✓	✓	✓	✓	✓
**Asymptomatic post-injury**			✓	✓	✓	✓	✓	✓	✓	✓	✓
**1-month post return to play post-injury**			✓	✓	✓	✓	✓	✓	✓	✓	✓
- Symptoms and activity assessed daily from the first assessment point until 7 days post return to play - Concussion Index completed following injury - Recovery Form completed following return to play - *Participant Satisfaction completed at 7-days post return to play*											

*QOL, Quality of Life; BSI-18, Brief Symptom Inventory 18 item; SAC, Standardized Assessment of Concussion; NPC, Near Point of Convergence; SCAT, Sport Concussion Assessment Tool*.

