### Planned Data Analysis

We conduct quarterly, interim analysis for descriptive outcomes to determine continued safety and feasibility of the study and to prepare safety reports.

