***Specific Aim 2*** (safety and feasibility): We will utilize descriptive statistics, qualitative analyses for open ended text of perceptions (exploratory based; triangulation) to understand overall safety, adverse event prevalence, and protocol perceptions.

***Sample size*** (determined based on primary outcomes): Given that each participant will be recruited between 6 and 48 h post-concussion and will be followed for a month after their return to play (average total time of ~37 days), if we estimate that each arm will have at least 100 participants, we will have 83% power to estimate an effect size of 0.64 in the MDR group as compared to the EGE group concerning days to asymptomatic. Table 4 shows the available power for varying sample and effect sizes.

**Table 4 T4:** Power and effect size based on number of participants in each arm.

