### Anticipated Outcomes

Outcomes from the ongoing trial will contribute to research efforts to better understand the effects of early rehabilitation and the current return to sport paradigm on recovery time. Research efforts like this ongoing trial provide a pragmatic framework for research that seeks to produce the highest-level evidence possible concerning management and treatment of SRC across sports and across various levels of play in differing medical care environments. Lastly, the study data will provide guidance to safely and effectively use early, active rehabilitation therapies in the current clinical landscape. In order to achieve these outcomes we expect to see a positive effect of the MDR and that both arms will illustrate both MDR and EGE to be safe and feasible. We anticipate then being able to develop implementation manuals and strategies to be used in a variety of clinical settings.

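### Safety under Specific Aim 2 has only a descriptive analysis; an arm difference with a site-clustered interval, on a measure collected alike in both arms, would be a cheap improvement

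*Protocol article*

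**What the plan says.** The Introduction gives two Specific Aims; the second is "2) evaluate the safety and feasibility of these protocols". Study Outcomes and Assessments lists the secondary endpoints as clinical and quality of life outcomes "as well as safety and feasibility outcomes".

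Planned Data Analysis treats these two groups differently. The modelled group is defined under Specific Aim 1: "For our secondary endpoints (clinical and quality of life measures), recovery trajectories will be examined by use of General Linear Mixed regression models", with random effects for site. Safety is handled under Specific Aim 2: "We will utilize descriptive statistics, qualitative analyses for open ended text of perceptions (exploratory based; triangulation) to understand overall safety, adverse event prevalence". The interim work is of the same kind: "We conduct quarterly, interim analysis for descriptive outcomes to determine continued safety and feasibility of the study".

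Two other places bear on how the safety results will be read. Safety Procedures says: "We specifically anticipated more discomfort among those in the multidimensional activity group". Anticipated Outcomes, in the Discussion, expects that "both arms will illustrate both MDR and EGE to be safe and feasible". The article gives no criterion for safe.

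**The concern.** The safety question is comparative in substance. The article predicts in which arm discomfort will be higher, and its Introduction cites concern that activity begun too early or too aggressively may worsen symptoms. Yet safety lies outside the set of outcomes for which the article names an arm comparison and an allowance for randomisation by site.

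If adverse event rates are shown by arm without a difference and interval, two similar percentages invite the conclusion that MDR adds no harm. At this sample size similar percentages are weak evidence of that, and the reader would not see how weak. What is at stake is the wording of the planned safety paper and of the implementation manuals that the authors hope to produce.

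**Working it through.** **The plan's own figure.** The only design calculation is 83% power for time to asymptomatic at 100 per arm and a hazard ratio of 4.5/7. With two-sided alpha 0.05 (assumed) and 12.5% attrition, the middle of the stated 10–15%, there are 175 events. Then √175/2 × |ln(4.5/7)| − 1.96 = 6.614 × 0.4418 − 1.96 = 0.96, which gives 83%. The figure reproduces, but it concerns a primary endpoint. The article gives no precision figure for safety.

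**Inputs for safety.**
- 100 to 200 injured participants per arm (Participants and Eligibility Criteria).
- 28 sites (Allocation to Study Arm).
- Event rate p: not given. The 10–25% in Safety Procedures is expected discomfort. I take 10% as an assumed event rate and show 5% and 25% as a range.
- Design effect DE: not given. I show 1 (no clustering), 1.5 and 2 as assumptions.

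**Formula.** 95% half-width of the arm difference = 1.96 × √(2p(1−p) × DE / n), with n per arm.

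For p = 0.10, n = 100, DE = 1: 1.96 × √(0.18/100) = 8.3 points. For n = 200: 1.96 × √(0.18/200) = 5.9 points.

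| Assumed rate | n per arm | DE 1 | DE 1.5 | DE 2 |
|---|---|---|---|---|
| 5% | 100 | 6.0 | 7.4 | 8.5 |
| 5% | 200 | 4.3 | 5.2 | 6.0 |
| 10% | 100 | 8.3 | 10.2 | 11.8 |
| 10% | 200 | 5.9 | 7.2 | 8.3 |
| 25% | 100 | 12.0 | 14.7 | 17.0 |
| 25% | 200 | 8.5 | 10.4 | 12.0 |

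**What a design effect implies.** With equal site sizes, DE = 1 + (m − 1) × ICC. Mean site size m is 200/28 = 7.1 or 400/28 = 14.3. DE = 2 then needs an ICC of 1/6.1 = 0.16 at the smaller size and 1/13.3 = 0.08 at the larger, so one design effect is not the same assumption at both sizes.

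**Does this leave a doubling open?** Suppose 10% is observed in both arms. On the difference scale with no clustering, the upper limits correspond to 10 + 8.3 = 18.3% and 10 + 5.9 = 15.9%, both below 20%. A doubling stays open only if DE exceeds (10/8.3)² ≈ 1.45 at 100 per arm or (10/5.9)² ≈ 2.9 at 200. On the ratio scale the upper limit is exp(1.96 × √(2 × 9/n)), that is 2.3 at 100 and 1.8 at 200 per arm. The answer depends on scale, size and clustering.

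**Are events counted alike in the two arms?** Safety Procedures defines a symptom-based adverse event as a rise of 10 or more points still present at the next session. EGE session logs start at Stage 2, after 24 hours asymptomatic. MDR sessions can start 24–48 hours after injury while symptoms remain, with at least two in Phase I and about four a week. MDR participants therefore have earlier and more numerous occasions on which an event can be recorded. A raw risk difference in session-based events would mix harm with ascertainment. Daily activity and symptom tracking, in contrast, is asked of all concussed participants in both arms.

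**The case against.** The strongest reply is that descriptive adverse event reporting is standard, that Aim 2 has no comparative hypothesis or margin, and that the layout of safety tables belongs in a full protocol or SAP, which is not shown. All of this stands. Rates by arm with a difference and interval fit within descriptive statistics, and the article plans a safety paper covering both arms. A reader might infer that the plan omits or forbids a comparison by arm; the text does not say so.

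A reader might also infer that raw prevalence would be the only basis for a safety conclusion. That is not so. Time to asymptomatic and time to clearance are compared between arms with a variance that allows for site, and symptom trajectories are modelled with site random effects. There is also outside oversight: "An independent safety officer reviews quarterly study safety reports". These analyses do not fully replace an event contrast, because average recovery can favour MDR while a minority has a persistent rise.

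Finally, the expectation that both arms will prove safe is a statement in the Discussion and not a decision rule. That an unsupported conclusion would follow is a risk and not a fact.

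**Conclusion.** The point holds as a cheap improvement to a stated method. The article names descriptive and qualitative analysis for safety, expects more discomfort in MDR, expects to call both arms safe, and names no arm difference, interval or criterion. At an assumed 10% event rate the uncertainty about the arm difference is about ±8 points at 100 per arm and ±6 at 200 before clustering. After clustering it is larger by a factor that the documents do not allow one to fix (±12 and ±8 if the design effect were 2).

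Two stronger readings are tempting and should not be adopted. One is that the trial could not exclude a doubling of adverse events: on the difference scale at 10% a doubling is excluded without clustering at both sizes, and at 200 per arm even with a design effect of 2. The other is that 10–25% is the adverse event rate: the article gives it for discomfort, which it regards as ordinary in rehabilitation, while an adverse event needs a large and persistent rise.

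**What to change.** Add to the SAP, or to the plan for the safety paper:

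1. Report adverse events and discontinuations of study treatment by arm, with the MDR minus EGE difference and a 95% interval that allows for clustering by site.
2. Base the main contrast on a measure collected the same way in both arms, such as a rise of 10 or more points on the daily symptom tracking that persists at the next entry. Fix the reference score and a common number of days, since tracking runs to 7 days after return to play and its length depends on recovery. Confirm that the daily survey carries the 22-item severity score, which the article does not state; without it the 10-point threshold cannot be applied to it.
3. Report session-based events per session by arm as supporting data, noting the different session schedules.
4. Word the conclusion by the excess that the interval excludes.

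The cost is a few lines, one table and a little more analysis, and the safety conclusion will be more guarded. No hypothesis test or added sample is needed, and no new data if the daily survey carries the symptom score.
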